**Discussion:**

There needs to be a greater understanding of the potential risks of the current treatment for older patients with subclinical hypothyroidism in a primary care setting. We will investigate the clinical importance of this issue and whether older subclinical hypothyroid patients have poorer outcomes when treated. Clarifying this concern may help address the healthcare resource implications of ageing patients being misclassified as having mild hypothyroidism, as these patients are more likely to repeat their blood tests. This could reduce prescription wastage and improve patient outcomes and quality of life in the ageing population.

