Previous studies that addressed the link between cardiovascular outcomes and LT4 treatment have failed to find a conclusive outcome. A cohort study on 1,642 patients aged over 70 years found no difference in cardiovascular events between treated and untreated groups [24]. The Thyroid Hormone Therapy for Older Adults with Subclinical Hypothyroidism (TRUST) study, a double-blind randomised placebo-controlled parallel-group trial of 737 adults aged 65 years and older with SCH, found no association between LT4 use and cardiovascular outcomes (hazard ratio 0.89; 95% confidence interval 0.47–1.69) [25]. The TRUST group concluded that LT4 should not be routinely prescribed to older people with SCH. Pooled results of the TRUST study and another randomised control trial found no significant difference in the cardiovascular risk of patients treated with LT4 versus those untreated [26]. However, both randomised controlled trials were underpowered due to small sample sizes. Most studies in older populations have not shown a clear association between SCH and cardiovascular events in patients aged over 65. The effect of mild thyroid failure on cardiovascular health becomes less evident with increasing age [27]. There is need for further large-scale studies investigating the impact of LT4 on cardiovascular health in patients over 50, particularly those aged between 50 and 65 years.

It is accepted that patients with overt hypothyroidism should be prescribed LT4 due to the association between the untreated condition and increased morbidity and mortality [28, 29]. However, the treatment of SCH is unclear due to a lack of reliable evidence in the past [30]. Over-treatment with thyroid hormones harms health, including poorer cardiovascular outcomes, atrial fibrillation, fractures, and osteoporosis [27, 31, 32]. However, over-treatment is common in older people and is associated with a longer time on replacement therapy and increasing age [33–35]. The European Thyroid Association guidelines recommend that SCH patients be prescribed LT4 when symptoms are shown and a TSH level is above 10 mIU/L [23]. It is also recommended that LT4 doses are personalised according to age, co-morbidities, and life expectancy [6]. However, research proves that these recommendations are not always followed [33].

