## Methods/Design

### Study aims

The study aims to evaluate whether LT4 benefits patients aged over 50 years with marginally raised TSH. The null hypothesis is that SCH patients over 50 years of age have the same bone health and cardiovascular outcomes when prescribed LT4 compared to those not prescribed LT4. The alternative hypothesis is that SCH patients aged over 50 years of age have worse bone health and cardiovascular outcomes when prescribed LT4 than those who are not prescribed LT4.

The objectives of the study are:

1) To use electronic healthcare records to undertake a cohort study comparing the cardiovascular outcomes (incident diagnosis of angina, myocardial infarction, stroke, peripheral vascular disease and stent/revascularisation procedure) between patients over 50 years of age with mildly elevated TSH levels prescribed LT4 versus those not prescribed LT4.

2) To use electronic healthcare records to undertake a cohort study comparing the bone health outcomes (incident diagnosis of osteoporosis, fragility fractures) between patients over 50 years of age with mildly elevated TSH levels prescribed LT4 versus those not prescribed LT4.

3) To use electronic healthcare records to undertake a cohort study comparing all-cause mortality outcomes between patients over 50 years of age with mildly elevated TSH levels prescribed LT4 versus those not prescribed LT4.

4) To use electronic healthcare records to undertake a target trial emulation study comparing the cardiovascular outcomes (incident diagnosis of angina, myocardial infarction, stroke, peripheral vascular disease and stent/revascularisation procedure) between patients over 50 years of age with mildly elevated TSH levels prescribed LT4 versus those not prescribed LT4 [46].

5) To use electronic healthcare records to undertake a target trial emulation study comparing the bone health outcomes (incident diagnosis of osteoporosis, fragility fractures) between patients over 50 years of age with mildly elevated TSH levels prescribed LT4 versus those not prescribed LT4.

6) To use electronic healthcare records to undertake a target trial emulation study comparing all-cause mortality outcomes between patients over 50 years of age with mildly elevated TSH levels prescribed LT4 versus those not prescribed LT4.

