### Study setting

THIN captures clinical data from general practices across the UK, holding anonymised records of approximately 6% of the UK population from 850 general practices. THIN has over 25 years of data recorded. To ensure a complete and reliable dataset, this project will capture data between January 1st, 2006, and December 31st, 2021. Preliminary counts from THIN show 530,792 patients with a TSH greater than 4 mIU/L. Preliminary counts also show 258,868 patients diagnosed with hypothyroidism within the same period. The variables that will be captured from the THIN database are as follows:

sex,diagnosed with hypothyroidism,date of diagnosis of hypothyroidism,date LT4 treatment commenced,first and last recorded LT4 dose,co-morbidities (heart disease, asthma, chronic obstructive pulmonary disease, diabetes, chronic kidney disease, rheumatoid arthritis, depression, dementia, dyslipidaemia, osteoporosis, fragility fractures).date of diagnosis of co-morbidities,current and past medications,date of death (if applicable),TSH, fT4, thyroxine (T4), triiodothyronine (T3), and free triiodothyronine (fT3) levels,date of recorded TSH, fT4, T4, T3, and fT3 levels,thyroid peroxidase antibody status,body mass index (BMI) at entry and end of the study period,blood pressure,smoking status.

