Confounding bias, immortal time bias, and information bias will be adjusted for both the cohort and target trial emulation studies [48]. In addition, selection bias and attrition bias will be adjusted for in the target trial emulation study. Confounding factors include sex, BMI, co-morbidities, and smoking status. The adjustment for confounding factors will be done using inverse probability weighting in the target trial emulation study [49]. In both studies, subgroup analysis will be done for each cardiovascular and bone health outcome and each age group (51–60, 61–70, 71–80, 81–90, 91 + years). A subgroup analysis including patients with a TSH level between 4 0.0 mIU/L and the upper limit of their age range in the TEARS study will be carried out. Another subgroup analysis of patients who have had a TSH level of 10 mIU/L or above or not will be conducted. Also, sensitivity analysis will be undertaken in both studies for different TSH thresholds, as the standard threshold can differ between laboratories. This study will perform a secondary analysis based on baseline fT4 levels, comparing patients with a low normal versus high normal levels (below and above median levels at baseline, respectively).

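### The primary composite and the bone outcome mix contact-dependent diagnoses with hard events, no named adjustment factor measures health-care contact, and nothing ties a harm conclusion to the hard-event results

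*Protocol article*

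**What the plan says.** All references are to the protocol article.

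- **Study setting.** The data are routine care records: "THIN captures clinical data from general practices across the UK". Dated thyroid tests and current and past medications are on the list of captured variables. Consultation counts are not.
- **Study aims.** The cardiovascular outcome, which is primary, is the "incident diagnosis of angina, myocardial infarction, stroke, peripheral vascular disease and stent/revascularisation procedure". The bone outcome, which is secondary, is the "incident diagnosis of osteoporosis, fragility fractures". All-cause mortality has its own objective in both studies. The alternative hypothesis is that "SCH patients aged over 50 years of age have worse bone health and cardiovascular outcomes when prescribed LT4" than without it.
- **Statistical analysis, sizing.** Sample size rests on 4.9% with LT4 against 5.4% without, 90% power and 5% alpha. This gives 82,118 patients for the cohort and 129,020 for the emulation.
- **Statistical analysis, bias.** "Confounding bias, immortal time bias, and information bias will be adjusted for both the cohort and target trial emulation studies". The confounders listed there are sex, BMI, co-morbidities and smoking status. The one adjustment technique named is inverse probability weighting, for confounding, in the emulation.
- **Statistical analysis, components.** Each cardiovascular and bone outcome is also to be analysed separately in both studies, under the label of subgroup analysis.

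**The concern.** Angina, peripheral vascular disease and osteoporosis enter a record when a patient consults or is tested. Infarction, stroke, fracture and death depend on this far less. With no common visit schedule, a patient seen more often has more chances of receiving the first kind of diagnosis.

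There is reason to expect more contact on LT4, since it is a repeat prescription with monitoring. The article gives indirect support. The abstract's discussion says of patients misclassified as mildly hypothyroid that they have extra testing ("as these patients are more likely to repeat their blood tests"). The Background states that "Over-treatment with thyroid hormones harms health, including poorer cardiovascular outcomes, atrial fibrillation, fractures, and osteoporosis", which could prompt a prescriber to look for those conditions in treated patients.

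Extra detection on LT4 would push the estimate towards the stated alternative and be read as harm. If LT4 in truth lowers events, as the sizing rates imply, it would mask that. The studies are large enough to detect a relative difference of about 9%, so a small distortion could matter. Weighting on sex, BMI, co-morbidities and smoking does not balance contact, and covariates measured at baseline cannot correct detection that diverges after treatment starts.

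**Working it through.** **1. The plan's own figure.** Inputs from the Statistical analysis section: p1 = 0.049, p2 = 0.054, power 0.90, alpha 0.05 (taken as two-sided).

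n per group = [1.960·√(2·0.0515·0.9485) + 1.282·√(0.049·0.951 + 0.054·0.946)]² / 0.005²
= (0.6126 + 0.4005)² / 0.000025 ≈ 41,059.

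This matches the stated 41,059 per group. The 1:4 calculation gives 25,805 + 103,220 = 129,025, against the stated 129,020. The sizing arithmetic is not in question. The target is a risk ratio of 0.049/0.054 = 0.907.

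**2. Model for differential detection.** Let s be the share of composite events that are contact-dependent and r the relative recording of those events on LT4. Both are assumptions, since the documents give neither.

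Bias factor b = 1 − s + s·r = 1 + s·(r − 1).

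- s = 0.20, r = 1.05: b = 1 + 0.20 × 0.05 = 1.01
- s = 0.30, r = 1.10: b = 1 + 0.30 × 0.10 = 1.03

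**3. No true effect (5.4% in both groups).** The observed LT4 risk is 0.054·b. The chance of a significant result in the harm direction, at a two-sided 5% level and 41,059 per group, is approximately Φ(difference/SE − 1.960).

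- b = 1.00: 2.5%
- b = 1.01: difference 0.00054, SE 0.00158, ratio 0.342; Φ(−1.618) ≈ 5%
- b = 1.03: difference 0.00162, SE 0.00159, ratio 1.020; Φ(−0.940) ≈ 17%

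At the emulation's 25,804 against 103,216 the figures are about 5% and 18%, so its design gives no extra protection on this point.

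**4. True benefit as sized (4.9% against 5.4%).** The observed risk ratio is 0.907·b.

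- b = 1.01: ratio 0.916, cohort power falls from 90% to 83%
- b = 1.03: ratio 0.935, cohort power falls from 90% to 62%

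**5. Why these are upper-end figures for the inputs chosen.** The model counts each extra diagnosis as an additional first event. Some of those patients would later have had an infarction, a stroke, a revascularisation or a later diagnosis, and would have been counted anyway. For them, earlier detection moves the date of the event and does not add one. The calculation also compares simple proportions, as the sizing does, although the planned analysis is a Cox model.

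**The case against.** Several points against the concern stand.

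- **No arm difference is documented.** The remark on repeat blood tests concerns ageing patients misclassified as mildly hypothyroid and does not compare LT4 with no LT4. Every included patient has a TSH above 4.0 mIU/L, so untreated patients may be retested too. The Background nowhere says that prescribers screen LT4 users. A reader might infer that the article shows more contact on LT4; it does not.
- **The missing method is not itself an error.** A reader might take the unexplained promise to adjust for information bias as the fault. This is a condensed article that cites a source for the promise, and the method may stand in a fuller document. The confounder list is also worded as open, and the abstract adds age and dosage.
- **Direction.** A reader might infer that extra detection could hide the effect being sought. The stated alternative is harm, and extra diagnosis on LT4 cannot hide that. It can only mask a benefit.
- **Larger numbers are available but unsupported.** With s = 0.30 and r = 1.20 the same formula gives b = 1.06 and a false-harm chance of about 53%. No figure in the documents supports those inputs over the lower ones, so they should not carry the argument.
- **Mitigation exists.** Infarction, stroke and fragility fracture will be analysed separately, and all-cause mortality is a named outcome in both studies.

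What this leaves is what the article itself fixes: a mixed primary composite, a mixed bone outcome, no contact measure among the named factors, and separate analyses that rank as subgroup or secondary with no stated bearing on how the composite is read.

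**Conclusion.** The concern holds in conditional form. If LT4 patients are seen or tested more, the primary composite and the bone outcome are open to detection bias towards apparent harm, or towards masking a benefit, and the named adjustment factors do not address it. The direction follows from the outcome definitions. The size does not, because it rests wholly on the assumed share and detection ratio. At the two illustrative settings the false-harm chance is about 5% or 17% instead of 2.5%. It stays at 2.5% if detection is equal, and the shift reverses if untreated patients are seen more. The hard-event and mortality results would help a careful reader to spot the problem, but the plan does not require anyone to consult them before concluding harm. This is a worthwhile, inexpensive improvement. It does not show that the planned result will be biased.

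**What to change.** In the Statistical analysis section:

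1. Name the already planned infarction, stroke and fragility-fracture analyses as key supporting analyses in both studies. Require a consistent direction there, read alongside all-cause mortality, before harm is concluded from the composite or the bone outcome.
2. Add contact before time zero to the weight model in the emulation and to the cohort model. Use counts of dated thyroid tests and of prescriptions, which are already captured, and consultation counts if they can be obtained. State that this handles baseline differences only.
3. Add one negative-control outcome that depends on contact but is not plausibly affected by LT4, to reveal differences in ascertainment after treatment starts.

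The cost is a few extra models, possibly one more code list, and wider intervals in the hard-event analyses because they have fewer events.

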**Methods:**

This project includes a retrospective cohort analysis and a target trial emulation study using electronic patient records collected between 2006 and 2021 and recorded in The Health Improvement Network database. The primary outcome of this study is to compare the cardiovascular outcomes of subclinical hypothyroid patients aged over 50 years treated with levothyroxine compared to those untreated. Secondary outcomes are bone health and all-cause mortality outcomes. Descriptive and inferential statistics will both be employed to analyse the data. Secondary analysis will explore confounding factors, including age, sex, smoking status, body mass index, co-morbidities, and levothyroxine dosage.

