The current literature suggests that older patients with mildly raised TSH concentrations may benefit from not being prescribed LT4 medication. The evidence is increasing and compelling to introduce age-specific TSH reference ranges for hypothyroidism regarding diagnostic thresholds and treatment targets to avoid patients being misclassified as having SCH and inappropriate treatment with thyroid hormones [13–15, 36, 37]. The distribution of TSH levels at the time of LT4 initiation has been described by Taylor et al., 2014 [33]. The median TSH when a patient is prescribed thyroid hormones has decreased from 8.7 mIU/L in 2001 to 7.9 mIU/L in 2009 in the UK, suggesting the likelihood a patient is prescribed LT4 treatment is increasing [33]. However, there has been a rising debate and emerging evidence suggesting that assessing borderline thyroid dysfunction may be more accurately characterised by fT4 levels rather than relying solely on TSH measurements [38, 39].

The literature is conflicting surrounding LT4 use and cardiovascular and bone health risk in the older population. A questionnaire answered by 408 individuals with SCH and taking LT4 found an increased risk of fractures in individuals over 50 years, particularly in the forearm [41]. It has also been found that the over-treatment of LT4 can increase the risk of cardiovascular morbidity, cardiovascular mortality and osteoporosis [42]. There is also conflicting evidence between the use of LT4 and mortality. The recent Baltimore Longitudinal Study of Ageing in 2021 found no association between all-cause mortality and LT4 use in over 65 year olds with normal TSH levels [43], while a much larger database study on 2,007,528 patients found that all-cause mortality was significantly higher in LT4-treated patients [44]. This suggests that LT4-based outcomes are dependent on both age and TSH levels.

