#### Inclusion criteria

Patients registered on the THIN database and aged over 50 on January 1st, 2006.Patients with a recording of TSH above 4.0 mIU/L between January 1st, 2006, and December 31st, 2021.Patients who are prescribed LT4 or receive no hormone replacement therapy. In the cohort study, patients in the treatment group will be prescribed LT4 before the end of the study period, December 31st, 2021. In the emulated target trial study, patients will initiate LT4 treatment and remain on it during a 5-year follow-up between January 1st, 2006, and December 31st, 2021. Patients in the emulated target trial study will be randomly assigned a strategy at baseline and be aware of their assignment.In the cohort study, patient follow-up ends at death, withdrawal from the database or December 31st, 2021, whichever occurs first.

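### The Methods list of confounders, which feeds the inverse probability weights, omits age, baseline TSH and baseline fT4 and conflicts with the abstract's list

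*Protocol article*

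**What the plan says.** The Statistical analysis section promises adjustment for confounding in both the cohort study and the target trial emulation. Its only list is: "Confounding factors include sex, BMI, co-morbidities, and smoking status". The next sentence gives the method: "The adjustment for confounding factors will be done using inverse probability weighting in the target trial emulation study". For the cohort, the section names Cox models and Kaplan-Meier curves but no separate covariate list.

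The abstract has a different list: "Secondary analysis will explore confounding factors, including age, sex, smoking status, body mass index, co-morbidities, and levothyroxine dosage". It adds age and LT4 dose and places the whole list under secondary analysis.

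Elsewhere in the Statistical analysis section, the three omitted variables are used only in side analyses:

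- Age: subgroup estimates for "each age group (51–60, 61–70, 71–80, 81–90, 91 + years".
- TSH: a subgroup up to the age-specific upper limit, threshold sensitivity analyses, and a split at 10 mIU/L: "Another subgroup analysis of patients who have had a TSH level of 10 mIU/L or above or not will be conducted".
- fT4: "This study will perform a secondary analysis based on baseline fT4 levels", divided at the median.

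Entry requires "Patients with a recording of TSH above 4.0 mIU/L between January 1st, 2006, and December 31st, 2021". Neither the inclusion nor the exclusion criteria set an upper TSH limit or require fT4 to be in range. The emulation also has a 1:4 matching ratio, with no matching variables named.

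**The concern.** An observational comparison of treated with untreated patients depends on its adjustment set. Here TSH defines eligibility and bears on the decision to treat, fT4 separates subclinical from overt disease, and age is an obvious determinant of cardiovascular events, fractures and death. A weight model built on sex, BMI, co-morbidities and smoking would balance none of the three except through their correlation with the listed factors.

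The conflict between the two lists adds to this. An analyst who follows the Methods leaves age out of the main estimate. One who follows the abstract includes age only in a secondary analysis, and there meets LT4 dose labelled as a confounder. At stake is whether the headline hazard ratios for cardiovascular events, bone health and mortality can be read as effects of LT4. With more than 80,000 patients, a modest bias would be reported with a narrow interval.

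**Working it through.** **1. Are the omitted variables confounders on the article's own account?**

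| Variable | Link to LT4 prescribing | Link to outcome |
|---|---|---|
| TSH | Background: guidance ties treatment to TSH above 10 mIU/L | Background: TSH above 10 mIU/L linked to coronary events, coronary death and heart failure |
| fT4 | Background: overt disease (low fT4) is accepted as needing LT4 | Background: higher fT4 associated with higher all-cause mortality in one cohort of people over 85 |
| Age | Indirect: Background says TSH rises with age | Not quantified; age gradient assumed below |

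The Background also reports that "The median TSH when a patient is prescribed thyroid hormones has decreased from 8.7 mIU/L in 2001 to 7.9 mIU/L in 2009". That is a time trend among treated patients. It does not compare them with untreated patients, so the guideline statements are the better support.

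The objectives speak of mildly elevated TSH, but the criteria have no ceiling, and the planned split at 10 mIU/L confirms that higher values are in the data. TSH and fT4 can therefore differ widely between the groups. The age bands run from 51 to 91 and over.

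**2. The plan's own sample size, reproduced.** Inputs from Statistical analysis: 4.9% v 5.4%, power 0.9, alpha 5% (taken as two-sided).

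n per group = [1.960·√(2·p̄·q̄) + 1.282·√(p₁q₁ + p₂q₂)]² / (p₁ − p₂)², with p̄ = 0.0515.

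This gives 41,060 per group and 82,120 in total (stated: 82,118). At 1:4 it gives 25,805 + 103,220 = 129,025 (stated: 129,020). Both agree apart from rounding. The formula has no confounder term, so changing the adjustment set leaves these figures unchanged.

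**3. Size of the effect sought.**

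- Risk ratio: 0.049 / 0.054 = 0.907.
- Hazard ratio, assuming proportional hazards: ln(1 − 0.049) / ln(1 − 0.054) = 0.905.
- Inverse: 1/0.905 = 1.105. A net bias factor of about 1.10 would cancel or mimic the effect.

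**4. Age gap that gives a bias of that size.** Gap in years = ln(1/0.905) / ln(1 + g), where g is the rise in hazard per year of age. The documents give no value, so g is assumed.

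| g (assumed) | Mean age gap |
|---|---|
| 3% | 3.4 years |
| 5% | 2.05 years |
| 7% | 1.48 years |
| 10% | 1.05 years |

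Using the risk ratio 0.907 instead gives 1.99, 1.44 and 1.02 years for the last three rows.

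**5. A binary factor of the TSH or fT4 type.** Bias = [p_T(RR − 1) + 1] / [p_C(RR − 1) + 1], where p_T and p_C are its prevalence in the treated and untreated. All inputs are assumed.

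- RR 2, prevalence 40% v 30%: 1.4/1.3 = 1.08
- RR 2, prevalence 50% v 30%: 1.5/1.3 = 1.15
- RR 3, prevalence 40% v 30%: 1.8/1.6 = 1.13

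The first falls short of 1.10; the other two exceed it.

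**6. Do the side analyses repair the main estimate?** No. A subgroup estimate within an age or TSH band limits confounding by that variable inside the band only. Ten-year bands still leave age differences within them. The overall hazard ratio is unaffected by having been subdivided.

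**The case against.** The strongest reply is that this is a condensed article. The list is introduced with open wording, so it need not be complete, and covariates in full are normally left to a statistical analysis plan that is not shown. The abstract does treat age as a confounder. The 1:4 matching in the emulation may use age or TSH. Age, TSH and fT4 all appear in planned subgroup, sensitivity or secondary analyses, so the authors have not ignored them.

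Much of this stands, and it rules out several stronger readings that a reader might infer:

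- That age has been deliberately excluded from the weights. The open wording and unnamed matching variables do not show this.
- That every hazard ratio is confounded by age and TSH. The banded estimates limit this within their own strata.
- That LT4 dose will be adjusted for in the treated-versus-untreated model. Dose is not in the Methods list, and the abstract only says it will be explored.
- That blood pressure and medications go unused. They are listed as captured, and absence from an open list does not show non-use.
- That age determines who starts LT4. No passage says so.

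What the reply does not remove is that the two lists in the same article disagree. A list that names BMI and smoking but leaves out age and the laboratory value that defines eligibility is stated badly, not merely shortened. Nor does the possible rescue by matching reach the cohort study, for which no matching is described.

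**Conclusion.** The point holds in limited form. The only confounder list in the Methods omits age, baseline TSH and baseline fT4, and it contradicts the abstract. Followed as written, the overall hazard ratios would be unadjusted for variables that the Background ties to prescribing and outcome (TSH and fT4) or to TSH itself (age). The exception would be matching in the emulation that happens to cover them.

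The planning effect is a hazard ratio of about 0.905. Under an assumed 5–10% rise in hazard per year of age, a mean age gap of about 2.0–1.0 years gives a bias as large. A reader might infer that the bias will exceed the effect. The documents do not support that: they give no age, TSH or fT4 difference between treated and untreated patients, and the direction is unknown. It is a possibility of relevant size, not a measured bias.

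Dose needs only a correction of wording. It exists only in treated patients and follows the start of treatment, so it cannot confound treated versus untreated.

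**What to change.** - State one adjustment set for both designs, measured at or before the index date: the listed factors (sex, BMI, co-morbidities, smoking status) plus age, TSH and fT4.
- Use this set in the emulation's weight model and in the cohort's Cox model.
- Say whether the 1:4 matching uses any of these variables.
- Bring the abstract and the Statistical analysis section into agreement, so that age is in the main adjustment and not only in a secondary analysis.
- Describe LT4 dose as an exposure characteristic examined among the treated, and remove it from the confounders.

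**Cost.** TSH and fT4 are already on the list of captured variables, and age is needed for eligibility. The stated sample sizes of 82,118 and 129,020 do not change. The weights will be slightly more variable, and some fT4 values will need imputation. The plan imputes up to 40% missing data and otherwise uses pairwise deletion; the documents do not give the share of missing fT4, so it should be checked before the model is fixed.

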#### Exclusion criteria

Patients aged 50 years or under on January 1st, 2006.Patients without a recording of TSH above 4.0 mIU/L between January 1st, 2006, and December 31st, 2021.Patients diagnosed with thyroid cancer, pituitary disease or hyperthyroidism.Patients prescribed medications such as amiodarone or lithium that can affect thyroid function.Patients who have undergone thyroid surgery or radioiodine treatment, suggesting previous thyroid dysfunction.Patients receiving a different form of thyroid replacement therapy to LT4, e.g. liothyronine or combination therapy with liothyronine and LT4.Patients with a baseline diagnosis of angina, myocardial infarction, peripheral vascular disease or stroke, where cardiovascular is the outcome variable.Patients with a baseline diagnosis of osteoporosis or fracture, where bone health is the outcome variable.

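### The TSH 10 mIU/L subgroup has no time point, so as worded it can sort patients on TSH values recorded after LT4 was started or withheld

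*Protocol article*

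**What the plan says.** In the protocol article, Statistical analysis, one planned subgroup reads: "Another subgroup analysis of patients who have had a TSH level of 10 mIU/L or above or not will be conducted". No date or window is attached. Shortly afterwards the same section says: "This study will perform a secondary analysis based on baseline fT4 levels", and it sets the fT4 cut at the baseline median.

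Three other parts of the article bear on this:

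- **Study setting** lists TSH results with their dates among the captured variables, for data from 2006 to 2021.
- **Inclusion criteria** admit a patient on any TSH above 4.0 mIU/L in that period. They end cohort follow-up at death, leaving the database or 31 December 2021. The emulated trial has a 5-year follow-up.
- **Exclusion criteria** anchor the cardiovascular item in time ("Patients with a baseline diagnosis of angina, myocardial infarction, peripheral vascular disease or stroke") and likewise the bone item. Other items carry no date: "Patients diagnosed with thyroid cancer, pituitary disease or hyperthyroidism", "Patients prescribed medications such as amiodarone or lithium that can affect thyroid function" and "Patients receiving a different form of thyroid replacement therapy to LT4, e.g. liothyronine or combination therapy with liothyronine and LT4". The surgery item points to history: "Patients who have undergone thyroid surgery or radioiodine treatment, suggesting previous thyroid dysfunction".

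**The concern.** A subgroup for a treatment comparison should be fixed by what is known at time zero. Whether a patient has ever reached a TSH of 10 depends partly on what happens later, and LT4 acts on TSH. The article itself links a lower LT4 dose with higher TSH (Background, on the group's feasibility study).

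Under an ever/never rule, an untreated patient whose TSH rises to 10 years after entry moves out of the never-10 group, while a comparable treated patient tends to remain. If the outcome also ends TSH recording, only patients who live long enough to be re-tested can move. Untreated patients who have the event early stay in never-10 and some untreated patients with long event-free time leave it. The untreated rate in never-10 then rises, and LT4 looks better there than it is. In ever-10 the distortion runs the other way.

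The never-10 group is the milder part of the population that the objectives describe, so its result is likely to be read closely. A ratio pushed below 1 there would work against detecting the harm stated in the alternative hypothesis.

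**Working it through.** **Plan's own figures.** The article gives no number for this subgroup. Its sample size reproduces (82,120 against 82,118 for the cohort; 129,025 against 129,020 for the emulation; two-sided 5%, power 0.9) and does not depend on this point. For scale, the planning rates of 4.9% and 5.4% give a ratio of 4.9/5.4 = 0.91.

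**Inputs.** The documents supply the end of follow-up, the 5-year emulation horizon and the outcomes. All the rates are assumptions: event rate h = 0.02/yr in both groups (no LT4 effect); untreated patients progress to TSH 10 at p = 0.02 or 0.05/yr, unrelated to event risk; treated patients do not progress; follow-up L = 10 years.

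**Step 1: the event ends TSH recording (death).** Write k = h + p. Per untreated patient entering, the never-10 group contributes:

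- events E = (h/k)[1 − exp(−kL)]
- person-years T = (h/k²)[1 − exp(−kL)(1 + kL)] + L·exp(−kL)

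The treated rate is h, so the rate ratio is h/(E/T).

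- p = 0.02: E = 0.1648, T = 7.473, rate 0.02206; ratio 0.02/0.02206 = **0.91**
- p = 0.05: E = 0.1438, T = 5.602, rate 0.02568; ratio 0.02/0.02568 = **0.78**

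**Step 2: only a fraction f of events ends TSH recording.** After a non-fatal event the patient stays in the database, and a later TSH of 10 still counts. Such a patient is never-10 only if TSH stays below 10 for all L years. For these events:

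- events E0 = exp(−pL)[1 − exp(−hL)]
- event person-years T0 = [exp(−pL)/h][1 − exp(−hL)(1 + hL)]

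Weight the event terms of Step 1 by f and these by 1 − f; the event-free term L·exp(−kL) is unchanged. Example with f = 0.3, p = 0.02: E = 0.1533, T = 7.436, rate 0.02062, ratio 0.97.

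| Share of events ending TSH recording (assumed) | p = 0.02 | p = 0.05 |
|---|---|---|
| 100% | 0.91 | 0.78 |
| 30% | 0.97 | 0.92 |
| 10% | 0.99 | 0.97 |
| 0% | 1.00 | 1.00 |

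**Step 3: other settings, same formulas.** With L = 5 years, the emulation horizon, the ratios are 0.95 and 0.88 at 100%, and 0.985 and 0.96 at 30%. With L = 10, 100%, and treated patients progressing at half the untreated rate, they are 0.95 and 0.88.

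**Step 4: simulation with different assumptions.** Assignment was random with no true effect. Assumed inputs were median TSH 6, LT4 lowering follow-up TSH by 20% or 40%, four yearly tests, 7% five-year risk, and a log hazard ratio of 0 to 0.4 per SD of latent severity. Splitting on any TSH up to the event gave ratios of 0.87–0.94 in never-10 and 1.13–2.42 in ever-10. Splitting on baseline TSH gave 0.97–1.06 at or above 10 and 1.00–1.02 below. This simulation also stops counting TSH at the event, so it supports the direction and the benefit of a baseline split, but says nothing about non-fatal events with continued testing.

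**The case against.** The strongest reply is that cohort follow-up ends at death, leaving the database or study end, not at a cardiovascular event. Many of the listed outcomes (angina, non-fatal infarction, stroke, revascularisation) leave the patient under observation with TSH still being measured. This stands. It is why 0.91 and 0.78 belong to death, or to any event that ends TSH recording, and cannot be carried over to the cardiovascular outcome. What survives for that outcome is the smaller effect in Step 2, plus an unsized distortion if TSH progression itself tracks risk.

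A second reply is that the wording could mean a history of TSH 10 at entry, and that the article promises to deal with immortal time bias in both studies and selection bias in the emulation. The first part is possible, but the sentence does not say so, while the nearby fT4 analysis does name baseline. The general promise does not repair a stated rule that sorts patients on post-baseline TSH; the weighting described covers sex, BMI, co-morbidities and smoking.

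A reader might also infer that the undated exclusions remove patients harmed by LT4. A hyperthyroidism code could follow over-treatment, and amiodarone could follow atrial fibrillation, which the Background lists as a harm: "Over-treatment with thyroid hormones harms health, including poorer cardiovascular outcomes, atrial fibrillation, fractures, and osteoporosis". The documents do not support that inference. Nothing says follow-up records will be used to exclude. The cardiovascular and bone items need the word baseline because those conditions are also outcomes, and a look-back window is detail that an article may leave to the full protocol.

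**Conclusion.** The point holds for the TSH 10 subgroup. As worded, the split has no time point, can use TSH values affected by treatment, and would favour LT4 in never-10 when there is no effect. The size rests wholly on assumed rates: about 0.91 to 0.78 over 10 years where the event ends TSH recording, as for all-cause mortality, and 0.95 to 0.88 over 5 years. For cardiovascular events it lies between those values and 1, and near 1 if most are non-fatal, testing continues and progression is unrelated to risk. The article does not say which outcomes this subgroup will cover.

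The stronger reading, that follow-up information decides who enters the study, is not supported. The split does not touch the primary comparison or the sample size. Nor is never-10 clearly the subgroup nearest the question: the one bounded by the TEARS age limits has at least as good a claim, and its text lacks the ever/never wording. The timing of the exclusions is a request for clarification, not an error shown.

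**What to change.** In Statistical analysis, define the TSH 10 subgroup by index TSH, or by the highest TSH up to time zero. For consistency, define the TEARS-limit subgroup in the same way. If an ever/never split is still wanted, label it descriptive and attach no treatment-effect interpretation.

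As a clarification only, state in Exclusion criteria that the undated items (hyperthyroidism and other thyroid or pituitary disease, amiodarone or lithium, other thyroid hormone) are applied to records up to time zero.

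The cost is a few words in two sections. Dated TSH results, dates of diagnosis and the LT4 start date are already among the captured variables, and the sample size does not change.
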